### Sample and recruitment

The sample size was calculated for 230 members of the Diabetes Association of La Rioja (ASDIR) aged 18 years or older and diagnosed with type 2 diabetes mellitus.

A 95% confidence level and a 5% margin of error were used, values commonly accepted in community intervention studies [22]. Additionally, a dropout rate of 15% was anticipated, in line with that observed in previous studies conducted with populations with type 2 diabetes in similar contexts, where dropout rates range between 10% and 20% during multi-month interventions [23–26]. This estimation takes into account factors such as advanced age, disease burden, and the potential for low adherence to behavioral change programs. With these parameters, the final adjusted sample size is 169 individuals. Through a sequential allocation process based on the order of informed consent signing, approximately half will be assigned to the control group (CG) and the other half to the intervention group (IG), resulting in 84 participants in the CG and 85 in the IG.

To make it known to the associated and to know their willingness to participate, the president of the association will proceed to send emails and a broadcast message on WhatsApp through the community group. The dissemination of the project will begin in April 2025 and will last a total period of two months. Those interested and who meet the inclusion criteria will be selected during the following month for the study. A face-to-face visit will be made to the Association to explain the detailed bases of the Project and to sign the informed consent, while the group allocation will be carried out simultaneously. The study will last for a total of 12 months from the date of informed consent signature. Fig 1 presents the flowchart outlining the planned process of sample selection, recruitment, and participant allocation for this study.

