### Statistical analysis

First, a descriptive analysis of the sociodemographic, clinical and anthropometric data of the participants will be performed. Quantitative variables (such as age, BMI, glucose, cholesterol and blood pressure levels) will be described using means ± standard deviation (for those with normal distribution) and medians (with 25^th^ and 75^th^ percentiles) when they do not follow a normal distribution. Qualitative variables (such as sex, educational level, and marital status) will be described as relative frequencies, cumulative relative frequencies, and percentages. These analyses will be performed using Microsoft Excel for data organization and IBM SPSS Statistics for statistical calculations.

The normality of quantitative variables will be assessed using normality tests, such as the Shapiro-Wilk or Kolmogorov-Smirnov tests, as appropriate. To evaluate the homogeneity of variances and sphericity in repeated measures, Mauchly’s test will be applied. To evaluate the efficacy of the intervention, the two groups of the study will be compared: CG and IG at different times (T0, T1, T2, T3). For continuous variables, a repeated measures analysis of variance (repeated measures ANOVA) will be conducted, applied only if the assumptions of residual normality and sphericity are met. In case of violation of the sphericity assumption, Greenhouse-Geisser or Huynh-Feldt corrections will be used to adjust the degrees of freedom. If the variables do not meet the normality assumption or the distribution is clearly non-parametric, the non-parametric Friedman test will be employed to analyze differences between repeated measurements.

The chi-square test will be applied to compare the distribution of qualitive variables between the two groups, such as the presence of comorbidities or the level of motivation to change. To establish statistical significance, a significance level of p < 0.05 will be used.

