Nevertheless, this study presents certain limitations that must be considered. Firstly, the single-center design may restrict the generalizability of the results to other populations or healthcare settings. However, despite its single-center nature, the sample includes a broad and diverse community of individuals with type 2 diabetes from across the La Rioja region, providing sociodemographic variability and thereby strengthening the external validity of the findings within similar populations.

Secondly, the absence of formal randomization in participant allocation may introduce a certain selection bias. However, since assignment was conducted sequentially based on the order in which informed consent was signed, some nonsystematic variability in participant distribution may have occurred, potentially helping to reduce this risk. Even so, absolute comparability between groups at baseline cannot be guaranteed, which may partially affect internal validity. To minimize this bias, homogeneous inclusion criteria were defined, and a standardized follow-up protocol was applied to all participants. This design aspect should be considered when interpreting the results, as some differences may stem from uncontrolled baseline characteristics in addition to the effects of the intervention.

Thirdly, given that participants in both the control and intervention groups may share community or healthcare environments, there is a potential risk of contamination between groups, which could diminish the true difference observed in the effects. Additionally, the lack of blinding of both participants and researchers—a common limitation in behavioral studies—may affect the objectivity of the results and should be taken into account when interpreting the findings.

Moreover, the 12-month duration of the study entails a potential influence of seasonal variation on physical activity and sedentary behavior levels, an aspect that should be addressed in future research.

Finally, it is recommended to conduct a prospective follow-up extending beyond the 12-month period covered in this study, as assessing long-term outcomes would allow for understanding the sustainability of behavior changes related to sedentary lifestyles, as well as their impact on clinical parameters in individuals with type 2 diabetes. Such longitudinal evaluation is essential to determine the enduring effectiveness of behavioral interventions in this population.

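### The Friedman fallback has no group term, so a non-normal sedentary-time or continuous clinical outcome would get no IG-versus-CG test

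*Protocol article*

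**What the plan says.** The Statistical analysis section of the protocol article frames efficacy as a between-group question: "the two groups of the study will be compared: CG and IG at different times (T0, T1, T2, T3". Continuous variables get a repeated measures ANOVA, "applied only if the assumptions of residual normality and sphericity are met". Greenhouse-Geisser or Huynh-Feldt corrections follow for failed sphericity. For failed normality, the only replacement named is that "the non-parametric Friedman test will be employed to analyze differences between repeated measurements".

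The same section has three other routes that bear on the point:

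- A chi-square test compares the groups on qualitative variables, with level of motivation as an example.
- Motivation and quality of life are to be analysed by repeated measures ANOVA or linear regression.
- Pearson correlation and multiple linear regression appear under the objective of relating sedentary time to changes in clinical parameters.

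The section closes by promising confidence intervals for the size of the effects. The Abstract names sedentary time (SBQ and accelerometer) and motivation as the primary outcomes.

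**The concern.** Friedman ranks the visits within each participant and asks whether the visits differ. It does not use group membership. Once an outcome is sent down this branch, the efficacy question in the same paragraph can no longer be answered by the named test.

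Two uses remain, and neither repairs this. Run separately in each arm, it yields two within-arm p-values and invites the reading that the intervention works because IG changed significantly and CG did not. Run on everyone, it asks only whether the whole sample changed. Neither gives an IG-CG effect estimate with a confidence interval.

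This matters most for sedentary time, which is a primary outcome and has no other stated comparison of the arms.

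**Working it through.** **1. Which outcomes have another between-group route?**

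| Outcome | Route if normality fails | Group term? |
|---|---|---|
| Sedentary time, SBQ and accelerometer (primary) | Friedman | No |
| Continuous clinical, anthropometric, biochemical | Friedman | No |
| Motivation scores (primary), quality of life | Linear regression also allowed | Possible |
| Motivation level as a category | Chi-square between groups | Yes |

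**2. Does Friedman carry group information?** On a simulated 169 by 4 data set, shuffling participants across the arms left the statistic unchanged (1.9207 before and after). This follows from the test itself and needs no assumption about the data.

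**3. Sample size used below.** The plan states "The sample size was calculated for 230 members of the Diabetes Association of La Rioja (ASDIR"), "A 95% confidence level and a 5% margin of error were used" and "a dropout rate of 15% was anticipated". With a proportion of 0.5 (assumed; not stated):

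n = 230 × 1.96² × 0.25 / (0.05² × 229 + 1.96² × 0.25) = 144.1, and 144 / 0.85 = 169.4.

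The stated 169 is reproduced, "resulting in 84 participants in the CG and 85 in the IG". After dropout this leaves about 144 / 2 = 72 per arm. The point does not depend on this figure.

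**4. Friedman per arm, same true change in both arms (no intervention effect).** Let p be the chance that Friedman is significant in one arm. For arms of equal size,

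P(IG significant, CG not) = p(1 − p), with maximum 0.5 × 0.5 = 25%.

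Simulation with 72 per arm, within-person correlation 0.6, drift profile 0 / 0.5 / 1 / 0.5 of the peak, and level 0.05 (correlation and drift are assumptions):

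| Peak drift (SD) | IG significant, CG not |
|---|---|
| 0.05 | 5.8% |
| 0.10 | 8.1% |
| 0.15 | 13% |
| 0.30 | 25% |
| 0.40 | 17% |
| 0.50 | 4.7% |
| 0.60 | 0.7% |

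A second simulation used log-normal data with 84 CG and 85 IG, log-SD 0.5, correlation 0.5 and a log-shift of 0.15 after T0 in both arms (all assumed). Per-arm rejection was 67.7% (IG) and 67.5% (CG). The formula gives 0.677 × (1 − 0.675) = 22.0%; the simulation gave 21.9%.

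**5. Friedman pooled, compared with a between-group rank test** (Mann-Whitney on the T0 to T2 change), same log-normal set-up:

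| Truth | Pooled Friedman rejects | Mann-Whitney rejects |
|---|---|---|
| Same drift in both arms | 94.6% | 4.3% |
| Arms move in opposite directions | 4.9% | 95.2% |

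The 94.6% is a correct detection of change over time. It becomes an error only if read as efficacy.

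**6. Could the branch be reached?** The documents give no outcome distributions. If an outcome were log-normal, Shapiro-Wilk at n = 169 would reject normality in 81%, 99% and 100% of samples for log-SD 0.2, 0.3 and 0.5.

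**The case against.** Several stronger readings are tempting, and the documents do not support them.

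- **Every non-normal outcome loses its comparison.** A reader might infer this from the fallback sentence alone. It does not hold for motivation, a primary outcome, or for quality of life. Both may be analysed by linear regression, and motivation level has a between-group chi-square.
- **About a quarter of null trials would mislead.** That is the ceiling of p(1 − p), reached only when the shared drift puts per-arm power near one half. The Discussion mentions only a "potential influence of seasonal variation on physical activity and sedentary behavior levels", with no size or direction. The plan also applies a Bonferroni correction, which lowers p. At 0.05/3 (three tests, assumed) the rate is 3.2% for a drift of 0.10 SD and 18% for 0.25 SD.
- **The sphericity wording is a second defect.** The condition and the sentence after it do not fit literally, but the usual corrections are named, the working rule is clear and no result changes. What to do when normality fails at some visits only is detail that an analysis plan normally settles.

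One could also argue that the multiple regression supplies the missing comparison. Its stated purpose, however, is covariate adjustment when sedentary time is related to clinical change, and it is not offered as a comparison of the arms on sedentary time. Nor can the gap be left to an unseen analysis plan, because the article names a specific test that cannot answer its own question.

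**Conclusion.** The concern stands for SBQ hours, accelerometer time and the continuous clinical, anthropometric and biochemical outcomes. If any of these fails normality, the plan as written gives no IG-CG test and no estimate of the difference. This rests on the structure of the Friedman test and on the text, not on simulation.

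The consequences depend on how the test is used. Per arm, with a shared drift and no intervention effect, the misleading pattern has probability p(1 − p): from under 1% to at most 25%, depending on a drift that the documents do not quantify. Pooled, the test can miss opposite changes almost entirely (4.9% against 95.2% under the assumptions shown). How many outcomes would reach the branch cannot be known from the documents. Because a primary efficacy comparison can disappear on the result of a normality test, the text should be changed before outcome data are seen.

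**What to change.** Replace the Friedman sentence with a between-group analysis for continuous outcomes that fail normality. Either of these is sound:

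1. A rank comparison of change from T0 between IG and CG: Wilcoxon rank-sum on the change, or rank ANCOVA on the T0 value.
2. The same group-by-visit model used for normal outcomes, with T0 included or adjusted for, and with a log transform or robust or bootstrap standard errors.

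In both cases report the IG-CG difference with a 95% CI. T0 must be in the analysis: allocation alternates without concealment (Group allocation and masking), and the Discussion accepts that baseline comparability is not assured. A model of T1 to T3 alone would carry any baseline imbalance into the group difference.

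The cost is a wording change and slightly more analysis work, with no new data.

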**Design and methodology:**

Quasi-experimental controlled study, single-center, parallel, two-branch, with a 12-month follow-up. We plan to recruit up to a total of 169 participants, who will be assigned in a 1:1 ratio to a control group (who will receive e-mails) and an intervention group (who will receive face-to-face group and individual visits and telephone calls). The active intervention has a duration of 6 months and will be carried out by nursing professionals. The primary outcomes are sedentary time measured with the Sedentary Behavior Questionnaire (SBQ) and the use of accelerometers, and the state of motivation to change measured through the Transtheoretical Model of Physical Exercise Change Questionnaire (TMPECQ).

**Trial registration.** ClinicalTrials.gov (NCT06893146).

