#### State of motivation to change.

Measured by the TMPEC questionnaire (S5 Appendix). This questionnaire aims to identify which stage of the transtheoretical model of change a person is in regarding his or her willingness to engage in physical exercise. The stages of change include precontemplation, contemplation, preparation, action, maintenance, and relapse. The questionnaire has items that use a respond scale from 1 (strongly disagree) to 5 (strongly agree) of reasons for not exercising, these items should only be completed by participants who do not exercise regularly. Similar items are rated in the table with the reasons why the participants perform physical exercise on a regular basis, the answers are rated on the same Likert-type scale from 1 to 5. The measurement of the questionnaire is performed by analyzing the average score of each corresponding stage of the transtheoretical model of change. Higher scores on each subscale of the questionnaire reflect a greater identification with the corresponding stage of behavioral change. Specifically, mean scores equal to or greater than 4 indicate a strong identification with that stage. A significant change can be interpreted as an increase of 0.5 points or more in the mean score of a subscale. Thus, increases in the mean scores of the preparation, action, and maintenance stages are considered indicative of progress in motivation toward the adoption and consolidation of regular physical exercise. Conversely, high scores on the precontemplation subscales reflect low readiness for change or resistance to modifying sedentary behavior. The internal consistency of this questionnaire shows Cronbach’s Alpha values>0.70 for each of the factors resulting from the factor analysis: precontemplation (0.71), contemplation (0.71), preparation (0.75), action (0.71) and maintenance (0.70) [43].

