Regarding the handling of missing data, a descriptive analysis will be conducted to identify its pattern and proportion. An intention-to-treat (ITT) analysis will be adopted, including all participants assigned regardless of their adherence or losses during follow-up. For quantitative variables with missing data, multiple imputation will be applied using the Multiple Imputation by Chained Equations (MICE) method, generating several complete datasets that will be analyzed to improve accuracy and reduce bias. Additionally, a sensitivity analysis will be performed comparing results from imputed and complete data to assess the robustness of the conclusions.

One of the objectives of the study is to evaluate how the reduction of sedentary time is related to improvements in clinical parameters such as glucose, lipid and blood pressure levels. To this end, Pearson correlations will be used to analyze the relationship between sedentary time (measured with accelerometers) and changes in these parameters. In addition, multiple linear regression models will be used to adjust the analyses for possible covariates (age, sex, antidiabetic treatment, etc.).

Subgroup analyses based on relevant participant characteristics (such as age, sex, and level of motivation to change) will be considered exploratory and conducted with the aim of identifying possible differences in response to the intervention. To control for multiplicity across primary and secondary outcomes, the Bonferroni correction will be applied to adjust the significance level and minimize false positives. Given the relatively small number of comparisons, this conservative approach is appropriate and unlikely to substantially reduce statistical power. Results from these analyses will be interpreted with caution.

Changes in quality of life and motivation to change will be analyzed using the corresponding validated questionnaires. Both will be analyzed using repeated measures analysis of variance or linear regression to determine whether the interventions have a positive impact on these aspects over time.

The reliability and validity of the instruments used, such as the SBQ and the ActiTrainer accelerometer, have been verified. These instruments will measure sedentary lifestyle in an objective and reliable manner. On the other hand, the internal validity of the MTCEJ and DQOL Questionnaire has also been evaluated by psychometric analysis.

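### The between-group test named for the level of motivation to change is an unordered chi-square, although progress is defined by direction and a second, score-based analysis is also named with no order of priority

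*Protocol article*

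**What the plan says.** The Abstract (Design and methodology) lists as a primary outcome, beside sedentary time, "the state of motivation to change measured through the Transtheoretical Model of Physical Exercise Change Questionnaire (TMPECQ").

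The Statistical analysis section gives this outcome two methods:

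- The chi-square test is to "compare the distribution of qualitive variables between the two groups, such as the presence of comorbidities or the level of motivation to change". No trend or ordinal version is named, and the sentence is not limited to baseline.
- Later, for quality of life and motivation: "Both will be analyzed using repeated measures analysis of variance or linear regression to determine whether the interventions have a positive impact".

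The section State of motivation to change describes the instrument:

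- Stages: "The stages of change include precontemplation, contemplation, preparation, action, maintenance, and relapse".
- Scoring: "The measurement of the questionnaire is performed by analyzing the average score of each corresponding stage of the transtheoretical model of change".
- Meaning of success: "increases in the mean scores of the preparation, action, and maintenance stages are considered indicative of progress in motivation".

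It gives no rule that places a person in one stage, and no rank for relapse. On significance, the plan says "a significance level of p < 0.05 will be used", with a Bonferroni adjustment whose divisor is not stated.

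**The concern.** The question is directional: do participants move towards preparation, action and maintenance? The test named for the categorical level asks something else, namely whether the mix of categories differs in any way between groups. It places an ordered outcome beside a nominal one (comorbidities) and spreads the evidence over four or five degrees of freedom.

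Three things are at stake. A forward shift can be missed more often than with a test that uses the order. A significant result cannot by itself be read as progress. And the test cannot adjust for the T0 stage, in a study with alternating, unconcealed allocation whose Discussion concedes that baseline comparability is not guaranteed.

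**Working it through.** **1. The plan's own figure.** The only sample size calculation is a finite-population precision formula, n = N·z²·p(1−p) / [e²(N−1) + z²·p(1−p)]. N = 230, e = 0.05, z = 1.96 for 95% confidence and 15% dropout come from Sample and recruitment; p = 0.5 is assumed.

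- Numerator: 230 × 3.8416 × 0.25 = 220.9.
- Denominator: 0.0025 × 229 + 0.9604 = 1.5329.
- n = 144.1, and 144.1 / 0.85 = 169.5, which reproduces the stated 169 (84 control, 85 intervention).
- After 15% dropout: 84 × 0.85 = 71.4 and 85 × 0.85 = 72.3, so about 71 and 72.

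The plan states no power, effect size or stage distribution for motivation. Everything below on power therefore rests on stated assumptions, at two-sided 0.05.

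**2. What the test can see.** Pearson's X² = Σ(O−E)²/E is unchanged if the stage labels are permuted. Moves forward, backward or to both ends can give the same value.

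**3. One worked case.** Assume five stages, controls spread evenly (20% each) and a proportional-odds forward shift with odds ratio 2.

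- Control cumulative odds 0.25, 0.667, 1.5 and 4 are halved. The intervention mix becomes 11.1, 13.9, 17.9, 23.8 and 33.3%.
- Chi-square noncentrality: (n₁n₂/N)·Σ(p₁−p₂)²/p̄ = (84 × 85 / 169) × 0.1486 = 42.25 × 0.1486 = 6.28. On 4 df the power is 49%.
- Linear trend with scores 0 to 4: mean difference 0.544, pooled variance 2.003, noncentrality 42.25 × 0.544² / 2.003 = 6.2. On 1 df the power is 70%.

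The noncentrality is almost the same; the extra degrees of freedom cause the loss. In general, a noncentrality that gives 70% on 1 df gives 48% on 4 df and 45% on 5 df; one that gives 80% gives 60% and 56%.

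**4. Simulation over a range** (20,000 trials per cell, power in %, chi-square against rank or trend test):

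| Odds ratio | 5 stages, 84/85 | 5 stages, 71/72 | 6 stages, 84/85 | 6 stages, 71/72 |
|---|---|---|---|---|
| 1.5 | 18 v 31 | 16 v 27–28 | 16 v 32 | 15 v 28 |
| 1.75 | 32 v 53 | 27 v 46 | 30 v 53 | 26 v 47 |
| 2 | 48 v 70 | 41 v 63–64 | 45 v 71 | 39 v 65 |
| 2.25 | 63 v 83 | 54 v 76 | 60 v 84 | 52 v 78 |
| 3 | 90 v 97 | 83 v 95 | 89 v 98 | 82 v 95–96 |

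The five-stage columns use a control mix centred on the middle stages, the six-stage columns an even one. Over all the control mixes tried, the gap at odds ratios 1.75 to 2.25 is about 18 to 27 points. At 1.5 or 3 it is about 7 to 16 points.

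**5. Rejection with no net progress.** Controls are even over five stages, 84/85 per arm. With intervention at 30/12.5/15/12.5/30% the mean stage is unchanged; chi-square rejects in 54% of trials, the rank test in 5%. With the milder 25/15/20/15/25% the figures are 18% and 5%.

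**6. Where the loss shrinks or reverses.**

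- Over odds ratios 1.5 to 3, the loss is about 5 to 18 points with four categories and 3 to 11 with three.
- With two categories the linear-by-linear statistic equals X²·(N−1)/N = X² × 168/169, so nothing material is lost.
- With controls at 25/30/20/15/10% and a non-proportional change, chi-square can win: 50% v 42–44% for 20/20/20/30/10%, and 60% v 12–14% for 25/15/35/15/10%.
- Under identical distributions all the tests hold about 5%.

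**The case against.** The strongest reply is that the directional question already has its own method. The words "to determine whether the interventions have a positive impact on these aspects over time" close the sentence that assigns motivation to ANOVA or regression, which work on scores and keep direction. This stands in part. A reader might infer that chi-square is the sole or deciding test of a primary outcome; the document does not support that. Nor does it say that the score analysis is the deciding one. Both are stated, unranked.

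Second, the variable in the power calculations is not defined in the plan. The instrument is scored as subscale means, and the only cut-offs given are a mean of at least 4 and a rise of at least 0.5. If the level is a yes/no version of either, the power argument vanishes. This stands, and it makes every power figure conditional. It also shows that the test is named for a quantity still to be defined.

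Third, the chi-square sentence could be descriptive, since it pairs motivation with comorbidities, and the plan elsewhere lists motivation level as a subgroup characteristic. That reading is possible. But the sentence carries no such limit and directly follows the paragraph on evaluating efficacy across T0 to T3.

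Fourth, a reader might take a loss of 20 to 25 points as a general property, or the polarised examples as false positives. Neither is right. The loss depends on the assumed shift and can change sign, and in the polarised examples the distributions truly differ. The fault there is in reading rejection as progress.

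The Bonferroni adjustment does not remove the gap. At 0.025, as if divided over two outcomes, with odds ratio 2 and 84/85, power is 36% v 60% with five stages and 34% v 61% with six.

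**Conclusion.** The concern holds in a limited form. The plan names an order-blind test, without baseline adjustment, for the categorical form of a primary outcome whose success it defines by direction. That mismatch does not depend on any simulation.

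The size does. The loss is roughly 18 to 27 points of power if the level is a five- or six-category stage, the shift is proportional-odds with an odds ratio of about 1.75 to 2.25, and 71 to 85 per arm are analysed. Outside those conditions it is smaller, nil or reversed.

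Because a score-based analysis of motivation is also stated, the outcome is not left without a directional test. This should be corrected before analysis, but it does not undermine the trial. The missing ranking of the two analyses and the undefined level belong to the same correction.

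**What to change.** In the Statistical analysis section:

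- Keep chi-square for nominal variables such as sex, marital status and comorbidities.
- Compare the motivation stage at the follow-up visits with a proportional-odds model containing study group and T0 stage, and report the common odds ratio of a more advanced stage with its confidence interval. At minimum, use a Mann-Whitney or linear-by-linear trend test.
- State whether this analysis or the score analysis (ANOVA or regression) is the primary one for motivation.

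In State of motivation to change, fix beforehand how the subscale means assign a person to one stage and where relapse ranks, with a sensitivity analysis that moves relapse.

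The cost is a few sentences of wording. No new data or visits are needed, and the model is available in SPSS, which the plan already names. The downside is small: the position of relapse has to be chosen without a rank from the document, and the proportional-odds assumption has to be checked.

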The results of the statistical analysis will be presented in tables and graphs to facilitate interpretation of the data, accompanied by confidence intervals to estimate the magnitude of the observed effects. Finally, the results will be discussed in relation to the existing literature on sedentary lifestyles in people with type 2 diabetes and the effectiveness of similar interventions.

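### Continuous outcomes switch to the Friedman test on a normality check: that branch gives no between-group estimate or interval, and the check can split across imputed datasets

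*Protocol article*

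**What the plan says.** All of this stands in the protocol article under Statistical analysis.

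- **Purpose.** Efficacy is to be judged by comparing CG with IG over T0, T1, T2 and T3.
- **Choice of test for continuous variables.** Repeated measures ANOVA is "applied only if the assumptions of residual normality and sphericity are met". If sphericity fails, "Greenhouse-Geisser or Huynh-Feldt corrections will be used to adjust the degrees of freedom". If normality fails, "the non-parametric Friedman test will be employed to analyze differences between repeated measurements".
- **Qualitative variables.** "The chi-square test will be applied to compare the distribution of qualitive variables between the two groups".
- **Missing data.** The analysis is intention-to-treat, "including all participants assigned regardless of their adherence or losses during follow-up". Gaps in quantitative outcomes are to be filled by MICE, and the plan describes that step as "generating several complete datasets that will be analyzed to improve accuracy and reduce bias". A sensitivity analysis sets imputed results against complete-data results.
- **Motivation and quality of life.** Linear regression is named as an alternative to repeated measures ANOVA.
- **Reporting.** Results will be "accompanied by confidence intervals to estimate the magnitude of the observed effects".

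The text does not say whether normality is checked on the observed data, once overall, or in each completed dataset.

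**The concern.** Two rules in the same section do not fit together.

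First, the fallback for non-normal data answers a different question from the one asked. ANOVA with a group-by-time term asks whether the arms change differently. Friedman asks whether the visits differ, ignoring arm. An outcome that fails a normality test therefore loses its efficacy comparison and its interval.

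Second, multiple imputation produces several versions of the same trial. A data-driven choice of test applied to each version need not choose the same test each time. If some versions go to ANOVA and others to Friedman, they share no quantity that can be combined.

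The outcomes exposed include sedentary time, a primary outcome (Abstract), by SBQ and by accelerometer. Imputation is likely to matter there. The article expects 15% dropout (Sample and recruitment), and each accelerometer record needs at least 4 valid days including a weekend day (Level of sedentary lifestyle). The analyst is the unblinded principal investigator (Group allocation and masking), so leaving the choice of test open until the data are seen is unattractive.

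**Working it through.** **1. The plan's own figure.** Inputs from Sample and recruitment: population 230, 95% confidence, 5% margin, 15% dropout. The proportion p = 0.5 is assumed.

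n = N z² p(1-p) / [e²(N-1) + z² p(1-p)] = 230 × 0.9604 / (0.0025 × 229 + 0.9604) = 220.89 / 1.5329 = 144.1

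144.1 / 0.85 = 169.5, which agrees with the stated 169 (84 CG, 85 IG) apart from rounding. These group sizes are used below.

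**2. What Friedman tests.** With n participants, k = 4 visits and R_j the sum of within-person ranks at visit j:

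Q = 12 / [n k (k+1)] × Σ R_j² - 3n(k+1), on k-1 = 3 degrees of freedom

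The group label appears nowhere. Reassigning every participant's arm leaves Q unchanged, so Q cannot measure an IG-CG difference. This needs no simulation and does not depend on missing data.

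**3. Simulation.** From the plan: 84 + 85 participants, four visits, 15% dropout. Assumed: between-visit correlation 0.6, monotone dropout, 20 imputations, both arms improving by 0.3 SD after T0, and 600 trials per row. Skewed data are lognormal with log-scale SD s and skewness (e^(s²)+2)√(e^(s²)-1), which is 3.023 × 0.151 = 0.46 for s = 0.15 and 3.064 × 0.254 = 0.78 for s = 0.25. The normality check is Shapiro-Wilk on T3 residuals in each completed dataset. A split means that some datasets of a trial pass and others fail.

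| Scenario | Normality check splits | Group-by-time rejects, D1 | Group-by-time rejects, D2 on the ANOVA F | Rubin 95% CI coverage, T3 change difference | Pooled Friedman rejects |
|---|---|---|---|---|---|
| No group effect, normal | 20.2% | 5.8% | 5.7% | 94.2% | 97.3% |
| 0.3 SD group effect, normal | 22.2% | 57.8% | 59.2% | 94.7% | 100% |
| No group effect, s = 0.15 | 56.5% | 6.2% | 6.0% | 96.2% | 97.8% |
| No group effect, s = 0.25 | 33.7% | 5.7% | 4.3% | 94.5% | 98.8% |

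D1 is the pooled Wald test and D2 combines the test statistics. The Monte Carlo standard error at 5% is √(0.05 × 0.95 / 600) = 0.9 percentage points.

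A separate simulation with correlation 0.55 and 800 trials gave normality splits of 25% with dropout only and 34% with a further 10% invalid records per visit (assumed). The D2-pooled ANOVA F rejected in 5.1% and 5.8% of null trials.

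**4. Reading the results.**
- The ANOVA branch pools validly: near-nominal error and coverage.
- If the check is repeated per dataset, splits are common: roughly 20-57%.
- With no group effect, Friedman is significant in 97-99% of trials, because both arms improve. It detects the time trend and is silent on the intervention. The exact rate depends on the assumed 0.3 SD trend.

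**The case against.** The strongest reply is that multiple imputation and the named ANOVA are compatible. ANOVA contrasts have standard errors and pool by Rubin's rules; F statistics pool by D1 or D2. This stands, and the table confirms it. A reader might infer that the plan can yield no valid pooled result at all; that is not so.

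Several other strong readings are also unsupported:

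- **Inflated type I error.** Simulated rates of 8.5% (dropout only) and 15.3% (plus 10% invalid records) arise when a single completed dataset is tested as if it were real data. The plan does not say that this will be done.
- **Chi-square.** It is planned for qualitative variables, and MICE for quantitative ones. The text does not pair them.
- **Larger split rates.** Counting disagreement on Mauchly's test as well gave 46-72% in one simulation. An epsilon correction only alters the degrees of freedom of the same F and leaves the contrast unchanged, so such splits do not change what is tested.
- **No pooling rule or number of imputations stated.** A condensed article commonly leaves these to the full protocol or SAP. This is no finding.
- **No poolable analysis named.** Linear regression is offered for motivation and quality of life, and its coefficients pool directly. It is not the stated group comparison for sedentary time.

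It is also fair to say that per-dataset checking is a possible reading, not a stated procedure. That limits the second part of the concern. It does not touch the first: Friedman is written into the plan as the fallback, and no pooling rule added later can supply a group effect that the test does not contain.

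**Conclusion.** The point holds in a limited form.

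**Certain, from the text and the formula:** a continuous outcome sent to Friedman has no IG-CG estimate, nothing to pool and no between-group interval. This contradicts the group comparison and the confidence intervals promised in the same section. MICE is not the cause; the defect exists with complete data.

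**Conditional:** if normality is checked in each completed dataset, datasets of the same trial can go to different tests, in roughly 20-57% of simulated trials. The range rests on assumed correlation, skew, dropout pattern and number of imputations. The article gives no distribution for its outcomes, so the rate in this trial is unknown.

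**Not shown:** that the ANOVA branch fails under imputation, or that the planned procedure has an inflated false-positive rate.

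It should be corrected before analysis. It is not a fault that must be resolved before the trial can proceed.

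**What to change.** Remove the normality-based switch to Friedman. For each continuous outcome, name one model in advance that contains group, visit and group-by-visit. An example is a linear mixed model on all observed records, adjusted for the T0 value, with a pre-stated transformation for skewed laboratory values. Report the IG-CG difference with its 95% CI.

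If MICE is kept, fit that same model in every completed dataset and combine the difference and its standard error by Rubin's rules, with no check in any dataset that changes the model. Pooling the group contrasts of the planned ANOVA would also be valid; the essential step is that one model with a group term is fixed for all datasets.

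The cost is analysis wording only: no extra data, visits or participants.
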